#### Step 2: pilot testing via a cluster randomized controlled trial (RCT)

To pilot test the enhanced intervention at EHS sites, we will compare the enhanced intervention’s feasibility, acceptability, and preliminary efficacy in improving maternal feeding styles and practices to EHS’ existing intervention. Prior to designing a larger trial, it is imperative to have data on recruitment processes (% eligible, reasons for not participating, recruitment yield), baseline process data (% completion, time range from recruitment to intervention, attendance/sessions completed), baseline survey data, and outcome data including preliminary effect sizes. These data will inform the sample size for a future RCT.

With EHS staff, we will identify two EHS sites and optimal dates/times during their regular monthly site-based group meetings for intervention implementation. Sites will be randomly assigned, via coin toss, to the treatment or control condition. The enhanced intervention will be implemented in a two-month period to align with the implementation of existing nutrition education. We will train an EHS staff person at each treatment site to deliver the enhanced intervention. At the control sites, existing nutrition education will be provided as usual.

Random selection will be used in which 15 mothers from both sites will be selected to participate (30 mothers total, 15 treatment and 15 control). This sample is appropriate for a pilot whose aims are to assess feasibility, acceptability, and preliminary efficacy [79]. EHS staff will recruit EHS-enrolled mothers as part of their regular outreach with program families, using the eligibility criteria for Phase 1.

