The research team will observe implementation for fidelity and qualitative debriefing interviews with five EHS staff members, including the implementers, to assess feasibility (e.g., fit with existing programming and program requirements, participant retention) and acceptability (e.g., format and length, cultural relevance). Members of the study team will attend the EHS group meetings to administer brief paper-and-pencil pre- and post-tests to participating mothers; these members will be blinded to the experimental control. At treatment sites pre-tests will be administered immediately prior to intervention implementation, and post-tests will be administered 1 month after the end of implementation. At control sites, the pre- and post-tests will be administered 3 months apart, in alignment with the treatment site data collection.

To determine preliminary efficacy, pre- and post-tests will assess increases in participants’ knowledge and use of responsive feeding styles and recommended feeding practices using the IFSQ and BBNQ; decreases in risky feeding practices using the BBNQ; increases in knowledge of the role of other caregiver feeding practices (based on results from Phase 1); and increases in use of recommended strategies for negotiating infant feeding with other caregivers (based on results from Phase 1 and Step 1 of Phase 2). Measures for the latter two outcomes will be developed by the research team. Post-tests of the treatment group will also assess the enhanced intervention’s acceptability (e.g., format and length), cultural relevance, and overall satisfaction (e.g., “In general, how satisfied were you with the intervention?”).

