We will consider the intervention feasible if qualitative analysis of EHS staff feasibility data (observations and debrief interviews) reveals no major concerns and at least 80% of intervention participants are retained at the post-test. We will consider the intervention to be acceptable if at least 80% of participants indicate that they were “satisfied” or “very satisfied” with the intervention. With regard to preliminary efficacy, our goal for the pilot is to determine whether the enhanced intervention positively impacts the proximal outcomes of feeding styles and practices and caregiver context, with the idea that if it does, it will positively impact on the distal outcomes of infant growth and obesity as tested in a future trial. Using quantitative analysis, we will assess pre- to post-test changes in outcomes in the treatment and control conditions, using general linear mixed models and/or permutation tests. We will consider the intervention preliminarily efficacious if the changes trend in the desired direction. The results of Step 2 will be the enhanced intervention and information on the feasibility, acceptability and preliminary efficacy of the enhanced intervention.

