Despite these limitations, our project stands to make important contributions by generating new knowledge about feeding styles and practices in multiple caregiver contexts and their relation to infant growth and obesity while integrating nutrition and obesity knowledge to enhance intervention. It fulfills our EHS partners’ priority of identifying risk factors for infants and toddlers in low-income families. If the pilot RCT proves efficacious and feasible, our next step will be to conduct a large-scale RCT with the long-term goal of wide dissemination of the intervention and engagement of WIC and other government-sponsored nutrition programs in the implementation of enhanced nutrition education to prevent obesity in early life. Through better understanding of how infant feeding styles and practices and other caregivers shape infant growth and obesity, and effective interventions that incorporate this understanding, we stand to reduce the exposure of children and the nation’s health care system to significant preventable comorbidity.

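### The pilot's preliminary-efficacy verdict rests on the sign of the changes alone, with no fixed contrast or number of outcomes, and the Discussion ties the large trial to it

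*Protocol article*

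**What the plan says.** All references are to the Protocol article. Step 2 of Phase 2 sets out a pilot cluster randomised trial. On clusters it says "we will identify two EHS sites", one assigned to each condition by coin toss, and on size "30 mothers total, 15 treatment and 15 control". One stated aim is to compare "preliminary efficacy in improving maternal feeding styles and practices to EHS’ existing intervention".

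Four groups of outcomes are measured before and after the programme, 3 months apart:
- "increases in participants’ knowledge and use of responsive feeding styles and recommended feeding practices using the IFSQ and BBNQ";
- risky feeding practices;
- knowledge of the role of other caregivers;
- strategies for negotiating feeding with those caregivers.

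The analysis sentence is "we will assess pre- to post-test changes in outcomes in the treatment and control conditions, using general linear mixed models and/or permutation tests". The decision rule follows at once: "We will consider the intervention preliminarily efficacious if the changes trend in the desired direction". In the same paragraph, feasibility requires at least 80% of intervention participants retained and no major concerns in the staff data, and acceptability requires at least 80% satisfied or very satisfied.

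The Discussion states the consequence: "If the pilot RCT proves efficacious and feasible, our next step will be to conduct a large-scale RCT".

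**The concern.** Feasibility and acceptability each have a numerical threshold. Efficacy has only a direction. The rule gives no size of change and no allowance for uncertainty. It does not say which outcomes count or how many must move, and it does not name the contrast whose direction is to be read. The same paragraph sets the pilot the goal of determining whether the programme improves the proximal outcomes, and a sign at this sample size cannot do that.

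Two things are at stake. An ineffective programme may be called preliminarily efficacious and carried towards a large trial partly on that label. And because the text admits several readings, the reading could be chosen once the results are known.

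**Working it through.** **Plan's own figure.** The document gives no error rate or power for this rule, so there is nothing to reproduce. The sample size agrees with itself: 15 + 15 = 30.

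**Inputs from the document.** 15 mothers per arm; one site per arm; four outcome groups; a 3-month interval; a direction-only rule.

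**Assumptions, because the document gives no figure.** Changes are approximately normal; correlation between outcomes is 0 to 0.8; favourable drift unrelated to the enhancement is 0 to 0.5 SD of the change score.

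**1. One outcome, treatment minus control, no effect.** The rule passes when the estimated difference has the right sign. By symmetry the probability is Φ(0) = 0.50, so the rule is a one-sided test at α = 0.5. Simulation with one site per arm and an intracluster correlation of 0, 0.05 or 0.2 gave 50.0%, 49.8% and 49.9%. Clustering does not alter this figure.

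**2. One outcome, treatment arm only, favourable drift d.** The pass probability is Φ(d√15). At d = 0.2, Φ(0.775) = 0.78.

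| Drift (SD of change) | Null pass rate, n = 15 |
|---|---|
| 0 | 50% |
| 0.1 | 65% |
| 0.2 | 78% |
| 0.3 | 88% |
| 0.5 | 97% |

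**3. Four outcome groups, no effect, no drift.** For independent outcomes:
- any one: 1 − 0.5⁴ = 0.94
- at least two: 11/16 = 0.69
- at least three: 5/16 = 0.31
- all four: 0.5⁴ = 0.06

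For a common correlation ρ, put p(u) = Φ(√ρ·u / √(1 − ρ)) and average the binomial probability with success probability p(u) over a standard normal u.

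| Outcomes required | ρ = 0 | ρ = 0.3 | ρ = 0.5 | ρ = 0.8 |
|---|---|---|---|---|
| Any one | 94% | 86% | 80% | 69% |
| At least two | 69% | 63% | 60% | 56% |
| At least three | 31% | 37% | 40% | 44% |
| All four | 6% | 14% | 20% | 31% |

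**4. All four required, treatment arm only, with drift.** Adding d√15 to the numerator of p(u) gives 37% (d = 0.2, ρ = 0) to 92% (d = 0.5, ρ = 0.5).

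**5. Would an interval-based go rule do better?** A natural substitute is to proceed if the 95% interval does not exclude a worthwhile difference. Assume baseline adjustment with a pre-post correlation of 0.5, and ignore clustering. The standard error is √(2 × 0.75 / 15) = 0.316 SD. With t(27) = 2.052 the half-width is 0.65 SD. The probability that an ineffective programme passes (non-central t) is:

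| Worthwhile difference | Null pass rate |
|---|---|
| 0.2 SD | 91% |
| 0.3 SD | 85% |
| 0.5 SD | 67% |

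For differences up to 0.5 SD this is more lenient than a sign on one outcome.

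**The case against.** **The control arm is not ignored.** A reader might infer from the rule that control does not enter. The documents do not support that. The sentence just before the rule says "we will assess pre- to post-test changes in outcomes in the treatment and control conditions", the section presents the pilot as a comparison with the existing programme, and control-site testing is aligned to the same interval. What stands is narrower: the rule does not say that the direction of the between-arm difference is what counts.

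**The rule is not always passed half the time or more.** A reader might also infer that from the 50% figure. It is true for one outcome, for an any-one or at-least-half requirement, or with enough favourable drift. It is false if all four groups must trend and there is no drift (6% to 31%), and the plural in the rule permits that reading. The defect is that the text does not choose.

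**Drift is an assumption.** The document gives no figure for it. Feeding practices may move either way as infants age, so risky practices could drift adversely. If the contrast is between arms, drift common to both cancels. The drift figures above show sensitivity; they are not expected values.

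**It is a pilot.** The section gives its purpose as process data and preliminary effect sizes to inform a later sample size, the label says preliminarily, and the Discussion requires feasibility as well. Leniency is common at this stage, which tempers the consequence. But the effect sizes can be reported without a verdict, and the Discussion speaks of the pilot proving efficacious.

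**An article condenses a fuller plan.** That would excuse an absent rule. Here the rule is stated, and stated in a form that cannot support its label.

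**Conclusion.** The point holds in limited form. The rule is a sign with no stated contrast and no stated number of outcomes. For one outcome, an ineffective programme passes 50% of the time, whatever the intracluster correlation. For four outcome groups the null pass rate runs from 6% to 94%, depending on how many must move and how they correlate. Reading the treatment arm alone raises it under favourable drift. The 50% rests only on symmetry; the four-group range also needs the assumed correlations; the figures above it for the treatment arm need the assumed drift.

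Making the contrast explicit would not by itself rescue the verdict. With one site per arm, any difference between sites is inseparable from the programme's effect, and an interval computed from individual mothers omits between-site variation. This pilot can give descriptive estimates and feasibility data, but not an efficacy verdict.

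**What to change.** - In Step 2, delete the sentence that declares preliminary efficacy. In the Discussion, remove the word efficacious from the condition for the large trial.
- For each outcome, report the treatment-minus-control difference at post-test, adjusted for the pre-test score, with a confidence interval.
- Label these estimates descriptive, and say why: one site per arm confounds site with treatment, and the interval leaves out between-site variation.
- Base progression on the feasibility and acceptability criteria already given in Step 2.
- Do not substitute a rule that the interval must not exclude a worthwhile difference as evidence of efficacy. At 15 per arm an ineffective programme would usually pass it for differences up to 0.5 SD.

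Cost: changes of wording, made before pilot outcomes are seen. The pre-test is already collected and no new data are needed. The effect sizes wanted for planning are still delivered, with their uncertainty shown. The price is that the pilot can no longer claim preliminary efficacy.

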#### Tracking and retention

To maximize retention, we will track participants through EHS records and align data collection with the regular EHS site visits. Focus group participants will receive $30. Working group participants will receive $75 for each meeting. Cognitive debriefing interview participants will receive $30. Pilot implementation participants will receive $25 at pretest and $35 at posttest. Pilot debriefing participants will receive $30.

## Discussion

Grow Well/Crecer Bien is a timely project, critical for addressing disparities in early childhood obesity. It innovatively moves beyond healthy eating to examine healthy feeding. In contrast with prior research, we conceptualize feeding as both a social and biological activity. Feeding provides an opportunity for people to fulfill social roles, transmits culture (e.g., consumption of culture-specific foods), and teaches behavioral norms [80, 81]. Therefore, we focus on the interactions between children and their caregivers, examining how children are fed (styles and practices) and why. Using the methods of feeding data debriefing and dyadic interviews, we focus on the interpersonal interactions between mothers and other caregivers as a contextual factor shaping infant feeding and, in turn, infant growth and obesity.

Our work acknowledges the role of other caregivers in infant feeding. US demographics have changed dramatically in recent years, [82] let alone since the development of nutrition interventions in the 1940s [83]. Existing interventions and programs tend to focus on single caregivers and do not formally incorporate other caregivers in nutrition education and programs [84, 85]. Furthermore, prior research on feeding focuses on the parents (usually mothers) in isolation, whereas this project focuses on mothers and trusted other caregivers. Using specific examples from the feeding data, collected through a well-known and user-friendly baby feeding app, and the dyadic interview data, we can understand who is involved in feeding, the roles and responsibilities of other caregivers in feeding, similarities and differences in feeding styles and practices among caregivers, and how feeding decisions are negotiated among caregivers. We will develop intervention components intended to enable mothers to better translate their nutrition education to practice in multiple caregiver contexts.

There is an urgent need to begin obesity prevention early in life [86, 87]. Despite EHS reaching a vulnerable and ethnically diverse population, few studies have incorporated obesity prevention with infants in this setting. There is an opportunity to integrate evidence-based feeding practices of the family system into EHS’ current programming. Rather than develop a new, separate intervention, we modify an existing intervention to translate to practice new knowledge about feeding in multiple caregiver contexts. Prevention scientists argue that building on existing interventions may be an ideal way to efficiently and cost-effectively address the need for prevention [88–90]. By using CBPR methods to modify an existing curriculum, we ensure that the enhanced intervention is feasible for EHS, the implementing organization, and acceptable to the target population.

We account for several potential limitations. Our research design involves building on Phase 1 findings. If unable to build on the findings, we will pull from the existing literature and relevant Phase 1 data to identify potential components for nutrition education and obesity prevention in early life to complete Phase 2. Additionally, other caregivers are currently not part of EHS programming. Were study participants to recommend an intervention component that includes other caregivers as participants in nutrition education, we could develop a component to include the participation of other caregivers as guests in an intervention session. This would enable other caregivers to receive education on feeding styles and practices between multiple caregivers. In this case we would modify the pilot test to also collect pre- and post-tests from other caregivers who receive the implemented component. It would be ideal to collect survey data from all trusted other caregivers as well as qualitative data from the full cohort. However, budgetary and time constraints limit our ability to carry out such data collection and analysis. Furthermore, Covid-19 has delayed the start of this project and recruitment and in-person data collection methods may need to be adjusted accordingly.

Despite these limitations, our project stands to make important contributions by generating new knowledge about feeding styles and practices in multiple caregiver contexts and their relation to infant growth and obesity while integrating nutrition and obesity knowledge to enhance intervention. It fulfills our EHS partners’ priority of identifying risk factors for infants and toddlers in low-income families. If the pilot RCT proves efficacious and feasible, our next step will be to conduct a large-scale RCT with the long-term goal of wide dissemination of the intervention and engagement of WIC and other government-sponsored nutrition programs in the implementation of enhanced nutrition education to prevent obesity in early life. Through better understanding of how infant feeding styles and practices and other caregivers shape infant growth and obesity, and effective interventions that incorporate this understanding, we stand to reduce the exposure of children and the nation’s health care system to significant preventable comorbidity.

## Data Availability

The datasets used and/or analyzed during the current study are available from the corresponding author upon reasonable request.

## Abbreviations

BBNQ: Baby basic needs questionnaire
CBPR: Community based participatory research
EHS: Early head start
IFSQ: Infant feeding style questionnaire
RCT: Randomized controlled trial
